### Sample size

We hypothesized that the ICT-based centralized monitoring group would be superior to the control group in terms of dose-taking compliance. A one-tailed test with a 0.05 significance level and 80% power provided a size of 51 in each group. With an estimated 10% dropout, the final sample size of 57 was determined (a total of 114 subjects, 57 in each group).

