### Secondary outcomes

The secondary outcomes in this trial include blood drug levels, immunological outcome, clinical outcome, patient satisfaction with the system, and the system stability and cost-effectiveness. The trough levels of tacrolimus and mycophenolic acid, creatinine level, and eGFR are measured at 4, 8, 12, 16, 20, and 24 weeks of follow-up. PRA is assessed at baseline and 24 weeks, and serum BK virus at 12 weeks. For clinical outcome evaluation, biopsy-proven acute rejection (BPAR) and graft loss developing during the follow-up are monitored. The patient Satisfaction Questionnaire is filled out at 4 and 24 weeks in the ICT-based centralized clinical trial monitoring group in order to assess how well the patients are satisfied with the system-enabled adherence management. The malfunction rate of the ICT-based centralized monitoring system is checked as well as any discrepancy between the smart pill box record and the patient-kept drug administration diary. Information about patients’ medication use sent to the ICT-based monitoring system is compared with the daily records of medication use written by the patients (type of medications used, number of pills ingested, and time of ingestion) to assess how closely they match. Stability is measured by using the following equation:$$ \frac{\mathrm{Number}\  \mathrm{of}\  \mathrm{pills}\  \mathrm{taken}\  \mathrm{over}\ \mathrm{a}\ \mathrm{certain}\  \mathrm{period}\  \mathrm{according}\  \mathrm{to}\  \mathrm{the}\ \mathrm{ICT}\hbox{-} \mathrm{based}\  \mathrm{centralized}\  \mathrm{monitoring}\  \mathrm{system}}{\mathrm{Number}\  \mathrm{of}\  \mathrm{pills}\  \mathrm{prescribed}\  \mathrm{over}\  \mathrm{the}\  \mathrm{sampling}\  \mathrm{period}\  \mathrm{according}\  \mathrm{to}\  \mathrm{the}\  \mathrm{daily}\  \mathrm{record}\  \mathrm{of}\  \mathrm{medication}\ \mathrm{use}}\times 100\%. $$

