### Statistical analysis

For categorical data, percent (%) is used for the number of subjects in a category against the total number of subjects. Analysis of categorical data uses the chi-square test or Fisher’s exact test. For continuous data, descriptive statistics (mean and standard deviation (SD)) are given, and the *t* test and the Mann-Whitney *U* test are used for analysis of normal distribution data and non-normal distribution data, respectively. The inter-group difference in adherence to immunosuppressants is assessed with the *t* test. Summary statistics of mean, SD, median, minimum value, and maximum value are presented for measurement data at each visit. The intra-group variation is analyzed with the paired *t* test or Wilcoxon’s signed rank test. Multivariate analysis is performed to identify clinical factors associated with drug compliance. Statistical significance is obtained with a *P* value of < 0.05.

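### The stated between-arm tests for eGFR and PRA ignore available baseline values; adjusting for them gains precision in secondary outcomes at no data cost, and within-arm P values should be dropped

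*Protocol article*

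**What the plan says.** All of the following is in the protocol article.

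- **Between arms (Statistical analysis).** One general rule covers continuous data: "the *t* test and the Mann-Whitney *U* test are used for analysis of normal distribution data and non-normal distribution data, respectively". No baseline covariate is named.
- **Within arms (same section).** "The intra-group variation is analyzed with the paired *t* test or Wilcoxon" signed rank test. The outcomes this applies to are not named.
- **Adjusted analysis (same section).** The only one stated is for adherence: "Multivariate analysis is performed to identify clinical factors associated with drug compliance".
- **Antibody outcome (Secondary outcomes).** "PRA is assessed at baseline and 24 weeks".
- **Kidney function (Secondary outcomes).** "creatinine level, and eGFR are measured at 4, 8, 12, 16, 20, and 24 weeks of follow-up". No baseline time is listed there for either measure. The entry criteria (Study participants) require an eGFR of at least 30 mL/min/1.73 m², so an entry eGFR has to be known for everyone randomised. A baseline creatinine is only implied.
- **Size (Sample size).** "A one-tailed test with a 0.05 significance level and 80% power provided a size of 51 in each group". An allowance of 10% for dropout then raises this to 57 per arm, 114 in all.

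**The concern.** Creatinine and eGFR are continuous secondary outcomes, so the general rule governs them. It also governs PRA if PRA is analysed as a continuous value. Patients may enter at any eGFR from 30 upward and at any time from 1 month after transplant, and their function must be stable. Wide spread between patients with stability within them makes it plausible, though the documents do not show it, that the entry value predicts much of the week-24 value. A comparison of raw follow-up values leaves that predictable variance in the error term.

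Separate paired tests ask whether each arm changed, not whether the arms differ. A significant result in one arm and not in the other is easily taken for a treatment effect, although it is not a test of one. At stake are wider intervals than necessary for the kidney-function and antibody comparisons, and a set of P values that do not answer the trial's question.

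**Working it through.** **1. The plan's own figure.** 51 / (1 − 0.10) = 56.7, rounded up to 57 per arm, so the stated 57 reproduces. The 51 comes without an effect size. Back-solving at one-sided 0.05 and 80% power gives (1.645 + 0.842) × √(2/51) = 0.492 SD. This concerns dose-taking compliance and is not affected by the present point.

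**2. Inputs for the check.** n = 51 evaluable per arm (Sample size). Two-sided 0.05 is assumed, because the Statistical analysis section gives P < 0.05 without sidedness. The baseline-to-follow-up correlation ρ is not in the documents; 0.3 to 0.9 is assumed. A true difference of 0.5 SD is used for illustration only.

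**3. Precision.** Take the variance of a t test on raw follow-up values as 1. Then:

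- ANCOVA variance = 1 − ρ²
- change-score variance = 2(1 − ρ)
- ANCOVA relative to change score = (1 − ρ²) / [2(1 − ρ)] = (1 + ρ)/2

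| ρ | ANCOVA variance | Cut against raw values | Change-score variance | Cut against change score |
|---|---|---|---|---|
| 0.3 | 0.91 | 9% | 1.40 | 35% |
| 0.5 | 0.75 | 25% | 1.00 | 25% |
| 0.7 | 0.51 | 49% | 0.60 | 15% |
| 0.8 | 0.36 | 64% | 0.40 | 10% |
| 0.9 | 0.19 | 81% | 0.20 | 5% |

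Against raw values the standard error falls by 1 − √(1 − ρ²): 28.6% at 0.7, 40% at 0.8 and 56.4% at 0.9.

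**4. What that means with 51 per arm.** The smallest difference detectable with 80% power is (1.960 + 0.842) × √(2/51) × √(1 − ρ²). The unadjusted sample needed to match ANCOVA is 51 / (1 − ρ²).

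| Analysis | Detectable difference (SD) | Power at 0.5 SD | Unadjusted n per arm to match |
|---|---|---|---|
| Raw values, unadjusted | 0.555 | 71.4% | 51 |
| ANCOVA, ρ = 0.3 | 0.529 | 75.4% | 56 |
| ANCOVA, ρ = 0.5 | 0.480 | 83.0% | 68 |
| ANCOVA, ρ = 0.7 | 0.396 | 94.2% | 100 |
| ANCOVA, ρ = 0.8 | 0.333 | 98.8% | 142 |

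**5. Within-arm tests.** If the true change is the same in both arms and each paired test is significant with probability p, exactly one arm is significant with probability 2p(1 − p).

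- Neither arm changes, p = 0.05: 2 × 0.05 × 0.95 = 9.5%.
- Both arms change by 0.2 SD (p from the noncentral t, n = 51): ρ = 0.5 gives p = 0.288 and 41%; ρ = 0.7 gives p = 0.440 and 49%; ρ = 0.8 gives p = 0.601 and 48%.
- The maximum is at p = 0.5: 2 × 0.5 × 0.5 = 50%.
- It falls again when power is high: a 0.3 SD change at ρ = 0.8 gives p = 0.913 and 16%.

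**The case against.** **The tests are valid.** Under randomisation the unadjusted t and Mann-Whitney tests are not biased by the omission of a baseline covariate. A reader might infer that the secondary comparisons are wrong or biased; the documents do not support that. This part of the objection stands in full.

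**The gain may be small.** No correlation is given, for PRA least of all, and the article does not say whether raw values or changes are compared. If changes are compared, the advantage of ANCOVA is only about 5% to 15% of the variance at ρ from 0.9 to 0.7. A reader might infer that adjustment is worth several times the sample. That needs both a high correlation and a raw-value comparison, and the documents establish neither.

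**No misuse is announced.** The article plans a between-arm test as well, and nowhere says that within-arm significance will count as an effect of the monitoring system. A reader might infer that such a conclusion is planned; it is not. The 50% is also the worst case. What remains is a caution about P values that serve no comparison.

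**Detail for the analysis plan.** The section is short, names neither eGFR, creatinine nor PRA, and belongs to a journal article. An analysis plan that is not shown may already adjust. But the point rests on the methods the article does state, and for continuous outcomes between arms it states only unadjusted tests.

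**Uneven baseline data.** Baseline PRA is explicit, entry eGFR follows from eligibility, and baseline creatinine is only implied. The schedule figure is not available here. If PRA is classed as positive or negative, the chi-square or Fisher rule applies and the figures above do not carry over. This also stands and limits the point.

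**Conclusion.** The point holds as a free improvement. For eGFR and PRA the stated between-arm comparison does not use a baseline value that exists. The cost is precision in secondary outcomes only. How much depends on a correlation that has to be assumed: adjustment is never worse at the correlations considered, and ranges from a modest gain (9% of the variance at 0.3, against raw values) to a large one (81% at 0.9), with a much smaller gain at high correlation if change scores were intended. These figures apply to roughly normal continuous outcomes with 51 evaluable patients per arm.

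The paired within-arm tests do not test a treatment effect. With no true difference between arms, they give a split result in about 9.5% of trials if nothing changes and in up to 50% if both arms change equally. They mislead only if they are read as evidence of effect.

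**What to change.** - Compare eGFR at week 24, or over the six visits, by ANCOVA or a mixed model with the entry value as covariate. Do the same for creatinine if a baseline value is recorded.
- Compare PRA at week 24 adjusted for baseline PRA, by logistic regression if it is analysed as positive or negative.
- Report the adjusted between-arm difference (or odds ratio) with its 95% CI.
- Show within-arm changes descriptively, without P values.
- State in the text when baseline eGFR and creatinine are measured.
- Centre as a further covariate is optional: neither the number of centres nor any stratification is stated.

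The cost is analysis-plan wording and code. No new measurement of eGFR or PRA is needed, and the sample size stays as it is.

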## Discussion

In KTRs, poor adherence to immunosuppressants has a direct link to graft loss which in turn results in deteriorated quality of life and increased healthcare costs both for individuals and the society as a whole. A systemic and scientific approach aimed at radically improving drug adherence is imperative. An electronic monitoring device has a proven clinical utility in checking and managing drug compliance. Its routine use in clinical practice, however, is unlikely due to the need for it to be linked to additional electronic equipments. There is no available clinical study conducted in Korea on the use of such an electronic monitoring device to manage adherence to immunosuppressants in KTRs. This study is the first of its kind in Korea to investigate how continuous use of the ICT-based centralized monitoring system could improve medication adherence in KTRs and how the improvement is associated with clinical outcome. Furthermore, the study seeks to assess the stability and cost-effectiveness of the ICT-based centralized monitoring system. It is well poised to make significant contributions down the road to maximizing graft performance and clinical outcome in KTRs.

Studies have reported on technology-based intervention for improving medication adherence among KTRs. In a recent study involving 120 KTRs, the patients were randomly subjected to adherence monitoring with customized reminders (including alarms, texts, phone calls, and/or e-mails), monitoring with customized reminders plus provider notifications (every 2 weeks, providers received notification if adherence decreased to 90% during that period), or wireless pill bottle use alone (control) to assess tacrolimus adherence [11]. The provider notification plus customized reminders group showed better medication adherence than all the other groups. Zanetti-Yabur et al. compared 21 KTRs who were using a mobile phone application to improve medication adherence with 53 control patients. Although they did not find any significant differences in medication adherence between the two groups, patients who used a mobile phone application showed higher adherence [17]. McGillicuddy et al. reported significant improvements in medication adherence after comparing a smartphone-based mobile health intervention group (*n* = 9) with a control group (*n* = 10) [18]. The use of pill boxes has been clinically shown to lower blood pressure and increase adherence to antiretroviral therapy not only in KTRs but also in patients with uncontrolled hypertension [19] and human immunodeficiency virus (HIV) infection [20].

Backed by rapid expansion in IT infrastructure, spread of the use of personal smart devices, and progress in u-Health technology, interest in the ICT-based clinical trial has been on the rise, and there indeed have been attempts at providing an ICT-based healthcare service. Around the globe, the incorporation of ICT into the clinical trial industry is in its infancy regarding developmental stage, and with little standardized system at present, there exists much room for further pioneering and development. This study is significant as it would pave the way for establishing the ICT-based centralized monitoring system necessary for effective management of drug compliance. Solid groundwork laid by this study might have broad implications for all other patient populations – recipients of other organ transplant, chronic suffers of hypertension, diabetes, or chronic kidney disease, patients with HIV infection, and tuberculosis patients, for example – for whom adherence to medication is undoubtedly critical in the course of treatment.

Despite the significance of its results, our study has the following limitations. First, we assumed that the reason for patients not taking their medications is unintended forgetfulness, and we investigated whether we could enhance adherence by providing the patients with reminder alarms from the ICT-based centralized monitoring system. However, this system does not use a camera to pictorially record the patients at the moment of medication ingestion; therefore, it cannot improve intentional non-adherence. To overcome this limitation, we will consistently educate our patients on the importance of medication adherence to reduce intentional medication non-adherence. In addition, we will use the BMQ-G to understand the reasons for patient non-adherence and find solutions to this problem. Second, even if patients ingest the correct amount of medications at the right time, there can be differences in drug level, or the secondary outcome, among the patients, owing to intra- and inter-patient variabilities [21, 22]. Therefore, it is rather difficult to use drug levels as the secondary outcome and they must be carefully interpreted.

To fully establish, expand, maintain, and effectively run an ICT-based centralized monitoring system for improving immunosuppressant adherence in KTRs in real-world health systems, it is necessary to use a standard framework such as the RE-AIM framework [16]. We plan to establish and evaluate the system via common and effective evidence-based interventions by using a standard framework.

### Trial status

The ICT-based randomized controlled clinical study was ongoing at the time of article submission in May 2017.

## Abbreviations

BPAR: Biopsy-proven acute rejection
CTMS: Comprehensive clinical trial management system
eCRF: Electronic Case Report Form
eGFR: Estimated glomerular filtration rate
HIV: Human immunodeficiency virus
ICT: Information and Communication Technology
KTRs: Kidney transplant recipients
PRA: Panel reactive antibody
RCT: Randomized controlled trial
RE-AIM: Reach, Effectiveness, Adoption, Implementation, and Maintenance
